#### Allocation concealment mechanism

We will use sealed, sequentially numbered, opaque envelopes, separated by each stratum. The randomization will be done after the inclusion of the child and after the radiographs. The group will be revealed for the examiners after the clinical examination.

#### Implementation

The examiner who performs the first clinical examination will see and designate the allocation of each child using the opaque envelops. Then, she will inform it only to the examiners who will perform the visual inspection and treatment plans.

#### Blinding (masking)

Children and their parents, as well as, the dentists responsible for the dental treatment, and the examiners who will evaluate the outcomes during the follow-up will be blinded regarding the allocation group.

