#### Caries detection procedures

The visual inspection will be done according to the International Caries Detection and Assessment System (ICDAS) [18]. The children will be positioned in a dental chair, under illumination, and they will receive prophylaxis using rotating bristle brush and a pumice/water slurry. The examiners will use a dental mirror and a ball-ended probe for the examination. The teeth will be examined wet, and then, they will be air-dried for 5 s with a 3-in-1 syringe. The examiner will also evaluate the caries activity status if a caries lesion is present [19]. The condition and treatment decision of each dental surface will be recorded on an appropriate form.

In all cases, the clinical evaluation will be performed without knowledge of the experimental group of the participant. After the examination, the examiner will be informed of the enrollment group and will plan the treatment with or without access to the bitewing radiographs.

For the children allocated to the experimental group, the same examination procedure will be done, but a visual inspection and radiographic examination will be used to reach the treatment decision. Radiographic evaluation will be performed using a light box.

The treatment plan elaborated according to the allocated group will be put in envelops that will be delivered for the dentists responsible for performing the dental treatment. On the first day of treatment, the children will receive orientation for oral hygiene and dietary advice, and an anamnesis will be performed with the parents of the children. Dentists will perform the dental treatment following the plan and according to the predetermined protocols for each type of treatment.

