#### Dental treatment protocols

The choice of the protocols of treatment is based on the best available evidence:Operatory treatments will be done with partial caries removal [20].High-viscosity glass ionomer cement will be used to restore cavitated active caries lesions in occlusal [21] or approximal [22] surfaces (score 4 of ICDAS or higher and/or lesions reaching the outer half of the dentin in the radiographic image).Resin-modified glass-ionomer cement will be used for restorations of lesions involving more than two surfaces [23].Non-cavitated active caries lesions will be treated with fluoride varnish [24].Prevention measure orientation will be based on the orientation of oral hygiene using fluoride dentifrice with 1000 to 1500 ppm of fluoride [25] and dietary advice [26].Endodontic treatment will use iodoform paste [27, 28].Dental extractions and other types of treatment will be provided.

The dentists responsible for the treatments will not receive the bitewings radiographs of the participants; they will only have access to periapical radiographs that may be useful for indirect pulp capping, endodontic treatment, and extraction.

During the operatory interventions, the presence of soft or hard carious tissue or the absence of carious tissue will be evaluated in order to record possible false-positive diagnosis for dentine caries.

The time required for all procedures and the materials used will be registered by an external examiner for the economic analysis. The time spent for each procedure, including return visits, will be considered in calculations of the direct and indirect costs.

The number of visits of each participant and the procedure done at each session, with their respective duration times, also will be recorded. For the calculation of direct costs, we will consider the average of market prices of the materials used in each procedure [29, 30]. Such values will be obtained by averaging the prices from different sources for the products being used, and these numbers will be updated during the study. For the calculations, indirect costs will be also considered, as described in previous studies [29, 30].

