#### Follow-up visits

After the end of the dental treatments, the children will be recalled every 6 months to reinforce the preventive orientations concerning the diet and biofilm control. Furthermore, the participants will be orientated to contact us in case of a new complaint. In this case, the additional treatment will be immediately made and registered.

After 12 and 24 months, the number of dental surfaces with dental treatment will be determined for all participants. For this, two different examiners, blinded in relation to the experimental group of the children, will evaluate the conditions and the need for new operative interventions. They will record the following:dental surfaces requiring operative treatment (evident dentine caries - cavitated or not);restored dental surfaces requiring replacement (large failures, caries around restorations, and the complete loss of the material will be considered);restored dental surfaces requiring repair (small failures); andteeth requiring endodontic treatment or extraction (in both cases, summing five surfaces per tooth).

Children with treatment needs will be treated by one of our dentists. All children will receive hygiene and dietary instructions, and fluoride products will be applied as needed. After 24 months, the ECOHIS will be reapplied for the children.

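### The treating dentists are called blinded, but an order to restore a surface visibly below ICDAS 4 probably reveals the radiographic arm, so false positives on those surfaces cannot be reported as assessed blind

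*Protocol article*

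**What the plan says.** Under Blinding (masking), the protocol article lists the treating dentists with the families and the follow-up examiners as masked, without qualification: "the dentists responsible for the dental treatment, and the examiners who will evaluate the outcomes during the follow-up will be blinded".

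Under Caries detection procedures it describes what these dentists receive: "The treatment plan elaborated according to the allocated group will be put in envelops that will be delivered for the dentists responsible". They are then bound by it: "Dentists will perform the dental treatment following the plan and according to the predetermined protocols for each type of treatment". The planning examiners also keep a surface-level record: "The condition and treatment decision of each dental surface will be recorded on an appropriate form".

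Under Dental treatment protocols, the criterion for a glass-ionomer restoration is "score 4 of ICDAS or higher and/or lesions reaching the outer half of the dentin in the radiographic image", while non-cavitated active lesions receive varnish. The safeguard stated for the treating dentists is that they do not see the bitewings.

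The same section explains how false positives are found: "During the operatory interventions, the presence of soft or hard carious tissue or the absence of carious tissue will be evaluated". The Outcomes section lists the number of false positives as a secondary outcome.

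**The concern.** The randomised intervention is the information used to write the treatment plan, and the plan goes to the person said to be masked. Withholding the bitewings hides the image but not its consequence. When the plan orders a restoration where the eye sees too little to justify one, the order itself points to a radiograph.

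This matters because the surfaces that may give the arm away are those on which a radiograph-driven false positive would be judged. Grading tissue as soft, hard or absent calls for judgement. The unmasking can run in one direction only, towards recognising the radiographic arm. The article also states its expectations openly. Its Background anticipates more false positives when radiographs are added, and its Discussion hopes to refute the recommendation for routine bitewings. If the tissue finding is influenced by knowledge of the arm, the likely direction is the expected one, and a report describing this outcome as blinded would overstate its protection.

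**Working it through.** No figure in the article bears on masking, so the check sets the sections side by side.

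1. **What can trigger a restoration.** Dental treatment protocols gives two routes, joined by and/or: a visual score of ICDAS 4 or higher, or a radiographic lesion in the outer half of dentine. A surface below ICDAS 4 fails the first route, so it can qualify only through the second, "lesions reaching the outer half of the dentin in the radiographic image".

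2. **Which arm has the second route.** Under Interventions, planners in the visual arm do not receive the bitewings. They may see periapical films when needed, for example to choose between endodontics and extraction, but only after the decisions on the other teeth have been made. If the protocol is followed, a restoration order on a surface below ICDAS 4 therefore belongs to the radiographic arm.

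3. **What the treating dentist can see.** The dentist has the order from the envelope and the tooth in the chair. If the surface visibly falls below ICDAS 4, comparing the two suggests the arm. Not seeing the bitewings does not prevent this.

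4. **How firm the inference is.** Planners are calibrated and score after cleaning, wet and then air-dried. Nothing says that the treating dentist repeats that scoring. A surface that looks milder to the dentist may have been scored 4 by the planner. The inference is probable, not certain.

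5. **What is judged at that moment.** The tissue evaluation that defines a false positive takes place during the operation. The operator exposes and sees the tissue. The sentence is in the passive and does not say who records the finding. The external examiner's stated task covers time and materials only.

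6. **What is not touched.** Follow-up visits assigns the 12- and 24-month assessments to two different examiners who are blinded to the group. A plan without a restoration below ICDAS 4 does not identify the arm by this route.

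**Size.** With 250 children in two arms, about 250 / 2 = 125 are in the radiographic arm. The share with at least one restoration order below ICDAS 4 is not given. Purely as an assumption, 5% to 50% would be 0.05 × 125 = 6.25 to 0.50 × 125 = 62.5, or about 6 to 63 children whose plan could reveal the arm.

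**The case against.** The strongest reply is that some inference from the plan is hard to avoid when the plan is the product of the randomised strategy, that it concerns one of several secondary outcomes in part of one arm, and that the article never says the operator records the tissue finding. A condensed article need not name the recorder or itemise the envelope, which may already list no more than surface and procedure. All of this stands. It limits the point but does not remove it: the masking statement is unqualified, and the article's own rules do not support it on these surfaces.

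Three stronger readings are tempting but unsupported.

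- **That unmasking is certain.** It is not, because the planner and the dentist may grade the same surface differently. The visual criterion is also a score, so the absence of an obvious cavity does not prove a radiographic order.
- **That the primary outcome is compromised.** Pain episodes are part of the primary outcome, and for a new complaint the article says "In this case, the additional treatment will be immediately made and registered". A reader might infer that an unmasked dentist's record feeds the primary outcome. That sentence names neither operator nor recorder. The statement that one of the team's dentists treats the child concerns needs already found by the blinded follow-up examiners. The route is speculation.
- **That the arms should be compared only on surfaces at ICDAS 4 or more.** Those surfaces meet the same visual criterion in both arms. The extra false positives that radiographs might cause lie mainly below 4, so this restriction would remove what the outcome is meant to count.

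**Conclusion.** The concern holds in a limited form. The unqualified statement that the treating dentists are blinded does not fit the article's own planning and treatment rules. For restorations ordered on surfaces below ICDAS 4, the operator can probably infer the radiographic arm, and the false-positive finding on those surfaces cannot be described as assessed blind. The primary-outcome examinations at 12 and 24 months are unaffected.

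The conclusion assumes that the restoration criteria are followed as written, and that the dentist can see that the surface falls short of ICDAS 4. It does not assume that the operator records the tissue finding, but the risk of bias is greater if so. Neither the number of such orders nor any resulting bias in the false-positive count can be estimated from the article. The point is worth correcting because it changes what may be claimed for an outcome central to the trial's rationale.

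**What to change.** - **Masking statement.** Under Blinding (masking), describe the treating dentists as not told the allocation, and add that masking is not assured for restorations ordered on surfaces below ICDAS 4.
- **Analysis.** Keep the overall between-arm comparison of false positives as the main one. Add a split by the baseline ICDAS score already recorded for each surface (4 or more, below 4), and label the below-4 results as potentially unmasked. If the rules are followed, the below-4 row should hold only radiographic-arm surfaces, so it describes that arm's contribution and is not a comparison. The number of children in that row would also supply the missing size.
- **Envelope.** For children still to be treated, keep the ICDAS score and the radiographic basis off the plan given to the dentist. This reduces the cue but cannot remove it, because the order itself remains. With 225 of 250 children included at submission, it reaches at most 250 − 225 = 25 further inclusions, plus any included children not yet treated.

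The cost is a less favourable masking statement and one extra table from data already collected. No new assessment is needed.

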### Data collection, management, and analysis

#### Data collection methods

Data collection and returning assessments will be made by researchers who have been trained to use ICDAS and to identify new dental treatment needs. They will be blinded to group allocation, and they will be the same examiners at all time-points for each participant in order to minimize inter-observer variability.

#### Data management

Clinical data will be entered directly onto predetermined sheets. Data quality will be ensured by validation checks that include missing data, out-of-range values, and illogical and invalid responses.

#### Statistical methods

For comparing the outcomes between the two groups, Student’s *t* test and Poisson regression analysis will be performed. With regard to the impact of Oral Health on quality of life, differences in the final and baseline scores will be compared between the groups through Student’s *t* test or the Mann–Whitney test, depending on the normality of the data distribution.

Multivariate analysis will be conducted to investigate the influence of the radiographic examination on treatment decision. Time and treatment cost will be compared by Student’s *t* test. An incremental cost-efficacy ratio will be used to compare the economic impact of both diagnostic strategies, considering both the initial examination and possible treatment and re-treatments during the study. The quality-adjusted life year (QUALY) will be also calculated in order to estimate the ratio of cost saved/spent by the use of the proposed diagnostic strategy. For all analyses, the level of significance will be set at 5 %.

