#### Outcomes

The primary outcome will be the number of dental surfaces with operative treatment needs in the follow-up. This outcome is composed of several mutually exclusive factors: number of surfaces with new dentin caries lesions; number of restored surfaces with necessity of replacement; tooth with pain episode and/or necessity of endodontic treatment and tooth indicated for extraction.

The separate components of the primary outcome will be considered as secondary outcomes. Other secondary outcomes will be the impact of oral health on quality of life, number of false-positive results, number of new lesions in the first permanent molars, cost-efficacy and quality-adjusted life year.

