#### Sample size

The sample size calculation was based on the occurrence of the primary outcome: number of dental surfaces of primary molars with operative needs during the follow-ups and the incidence data. Considering operative needs, we observed a mean of 17.6 surfaces with new caries lesions after 2 years [31], approximately 10 % restoration failure of occlusal or occluso-proximal restorations in 2 years [32], 0.08 extracted teeth in 2 years, with 0.2 surfaces [33] and 0.3 pain episodes in 2 years, with one surface [33].

Therefore, a mean of 19 surfaces with treatment need in the visual inspection alone group is expected. A difference of five surfaces with treatment need in the visual plus radiographic method group was considered as a minimally clinically important difference. The standard deviation values expected for visual and visual plus radiographic groups were 15 and 10, respectively. Therefore, using a two-tailed test and considering a significance level of 5 % and 80 % power, the minimum sample size of children calculated was 103 per group. Anticipating an attrition rate of 80 %, the final minimum sample size was 250 children for the entire study.

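### Poisson regression is named without an overdispersion correction for a count planned with variance far above its mean, and the protocol does not say whether it or the t test decides

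*Protocol article*

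**What the plan says.** The primary outcome is a count per child (Outcomes): "The primary outcome will be the number of dental surfaces with operative treatment needs in the follow-up".

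Statistical methods names two procedures for comparing the outcomes between groups, Student's *t* "test and Poisson regression analysis will be performed". It ranks neither above the other and does not mention overdispersion, robust standard errors or a negative binomial model. For quality of life the same section does give a rule for choosing between two tests, based on normality. It gives none for the primary count.

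The Sample size section sets out the distribution expected for that count:
- Mean: "a mean of 19 surfaces with treatment need in the visual inspection alone group is expected".
- Difference: "A difference of five surfaces with treatment need in the visual plus radiographic method group was considered as a minimally clinically important difference". The direction is not stated.
- Spread: "The standard deviation values expected for visual and visual plus radiographic groups were 15 and 10, respectively".
- Error rates: "using a two-tailed test and considering a significance level of 5 % and 80 % power".
- Result: "the minimum sample size of children calculated was 103 per group".

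**The concern.** Poisson regression in its ordinary form takes the variance of the count to equal its mean. A Poisson count with mean 19 has an SD of √19 = 4.4, and one with mean 14 an SD of √14 = 3.7. The trial was sized on SDs of 15 and 10. The named model, read plainly, therefore contradicts the variance that the protocol itself expects.

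When the variance is understated in this way, the estimated rate ratio is unaffected, but its standard error, confidence interval and p-value are wrong, and always in the direction of too much certainty. The trial is meant to support or overturn guideline advice on bitewing radiographs, so a false difference or a falsely narrow interval on the primary outcome would bear directly on its conclusion. With two tests named and no order between them, a report could rest on either one.

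**Working it through.** **Inputs** (Sample size section): means 19 and 14, the latter assuming the five-surface difference is a reduction; SDs 15 and 10; two-sided 5%; power 80%; 103 per group.

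**1. The planned sample size reproduces.** For a comparison of two means:

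n = (15² + 10²) × (1.96 + 0.84)² / 5² = 102.04, rounded up to 103 per group.

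This matches the stated figure, so the SDs are the working basis of the design, and the calculation is that of a test of means.

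**2. Dispersion (variance divided by mean).**
- Visual alone: 225/19 = 11.8.
- Visual plus radiographic, mean 14: 100/14 = 7.1.
- Visual plus radiographic, if the mean were 24 instead: 100/24 = 4.2.

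**3. Standard error of the log rate ratio at 100 per arm.**
- Model-based Poisson: √(1/1900 + 1/1400) = 0.035.
- From the planned SDs: √(225/(100 × 19²) + 100/(100 × 14²)) = 0.106.
- The ratio is 3.0. It does not depend on the number per arm, because both standard errors shrink with √n.

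**4. Confidence interval for the planned ratio 14/19 = 0.74.** With ln(0.74) ≈ −0.305:
- Model-based: exp(−0.305 ± 1.96 × 0.035) = 0.69 to 0.79.
- Correct: exp(−0.305 ± 1.96 × 0.106) = 0.60 to 0.91.

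**5. Type I error of the nominal 5% Poisson test.** With dispersion φ, it is 2 × (1 − Φ(1.96/√φ)):
- φ = 11.8: 57%.
- φ = 7.1: 46%.
- Equal means of 19 with SDs 15 and 10, so φ = (225 + 100)/(2 × 19) = 8.6: 50%.
- φ = 4.2: 34%.

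**6. Simulation check.** 20,000 null trials per setting, negative binomial counts, 103 per arm, two-sided 5%:

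| Null setting | Poisson, model-based | Poisson, robust | Quasi-Poisson | t test |
|---|---|---|---|---|
| mean 19, SD 15 in both arms | 56.5% | 5.3% | 5.2% | 5.0% |
| mean 14, SD 10 in both arms | 46.6% | 5.3% | 5.2% | 4.9% |
| mean 19, SDs 15 and 10 | 50.2% | 5.1% | 5.0% | 4.9% |

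**7. How often the two named tests would disagree with no effect.** The share of trials with Poisson significant and the t test not is at least the difference between their rejection rates: 56.5 − 5.0 = 51%, 46.6 − 4.9 = 42%, and 50.2 − 4.9 = 45% in the three settings.

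**8. Power at 19 against 14, 103 per arm.** Robust Poisson 82%, quasi-Poisson 82%, t test 81%.

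**The case against.** The strongest reply is that the article names only a model family. Poisson regression with a robust or quasi-Poisson variance is still Poisson regression, the variance estimator is often left to an analysis plan, and that plan is not shown. This stands as a condition: the error rates above apply only if the usual model-based standard errors are used. It does not dispose of the point. The concern is not that a detail is absent, but that the named model, in its plain reading, conflicts with the variance stated in the same article, and nothing there corrects it.

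Second, a valid test is already planned. The t test holds about 5%, is listed first, and matches the sample-size calculation. That also stands. A reader might infer that a trial with no effect would be declared positive about half the time. The document does not support this as a statement about the whole trial: it would follow only if model-based Poisson regression were allowed to decide, alone or as one of two routes to significance, and the article says neither.

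Three further limits are fair:
- The ratio of 7.1 rests on a radiographic mean of 14. At a mean of 24 that arm's ratio is 4.2, which is smaller but still far from 1.
- Teeth needing endodontics or extraction count five surfaces each (Follow-up visits: "in both cases, summing five surfaces per tooth"). It is tempting to add this as extra overdispersion, but the planned SDs describe the composite and probably already include it. It would also be small for extractions: at the planned 0.08 extracted teeth, taking their number as Poisson, it adds about 0.08 × 25 = 2 to a variance of 225.
- No SDs are given for the component counts, so the ratios of 7 and 12 cannot be carried over to them.

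**Conclusion.** The point holds for the Poisson p-values and confidence intervals of the primary outcome. On the protocol's own planning values, ordinary Poisson regression would report a standard error about one third of the correct size and would reject a true null hypothesis in about 46% to 57% of trials at a nominal 5%. The t test is not affected. The remaining gap is that the article does not say which of the two decides, although with no effect they would conflict in at least four trials in ten.

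This rests on three assumptions: model-based standard errors are used; the planned SDs of 15 and 10 are roughly right; and, for the lower end of the range, the five-surface difference is a reduction.

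**What to change.** In Statistical methods, state that Poisson regression will use robust (sandwich) standard errors or a quasi-Poisson variance, or replace it with negative binomial regression. In the same sentence, name one analysis as primary for the child-level count and make the other supportive. Either the t test or the corrected count model would serve; the t test need not be demoted. Use the same overdispersion-robust variance for any component count analysed by Poisson regression, as a safeguard, since no figures for the components are given. If an analysis plan already specifies this, the published description should be brought into line with it.

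The cost is one sentence and standard software. Poisson confidence intervals become about three times as wide on the log scale, which is their correct width. No larger sample is needed, since power at the planned difference stays at about 81% to 82%.

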#### Interventions

An initial clinical examination will be performed to evaluate the teeth present in the mouth, as well as the caries experience using the World Health Organization criteria [14]. The children will be classified in subgroups according to age (3 and 4 years old or 5 and 6 years old) and according to the caries experience (children with decayed-missing-filled-surfaces (dmf-s) less than or equal to 3 or children with dmf-s greater than 3).

If the child is eligible to participate in the study, bitewing radiographs will be taken from each side, including the upper and lower primary molars (two bilateral radiographs for each child), as recommended by different clinical guidelines throughout the world [5–7]. Complementary periapical radiographs also will be taken when necessary. Radiographs will be processed using the time/temperature method, in which the film stays in the revealing solution (Eastman Kodak, Rochester, NY, USA) for 2 min at a temperature of approximately 27 °C [15], followed by a fixation time of 10 min in fixing solution (Eastman Kodak, Rochester, NY, USA), and then by washing in water for 20 min [15]. The revealing and fixing solutions will always be new, replaced at the beginning of each period of clinical appointments, guaranteeing the quality of processing.

In addition, a questionnaire to evaluate the impact of oral health on the quality of life of the children at baseline will be applied for the parents. The instrument used will be the Brazilian version of the Early Childhood Oral Health Impact Scale (ECOHIS) [16, 17]. Then, the participant will be randomly allocated in one of the two groups.

The groups will be defined according to the diagnostic strategy used for reaching the treatment decision related to dental caries in primary molars proposed for each child. The two groups are as follows:Visual inspection alone: The treatment decision plan will be based only on a visual inspection. The examiners will not receive the bitewings of these children to elaborate the treatment plan. They will only access periapical radiographs when necessary (to decide between endodontics or tooth extraction, for example); those radiographs will be available after the decision regarding the process for the other teeth has been rendered.Visual inspection plus radiographic: The treatment plan will be based on the visual inspection complemented by radiographic examination. The access to periapical radiographs is also permitted in this case.

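### The ECOHIS comparison uses unadjusted change scores and a test chosen by normality; adjusting for the baseline already collected is more precise than the t test on change and fixes one effect measure

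*Protocol article*

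**What the plan says.** The Statistical methods section of the protocol article deals with quality of life in one sentence: "differences in the final and baseline scores will be compared between the groups", using Student's t test or Mann–Whitney, "depending on the normality of the data distribution". It names no baseline covariate for this outcome. The Poisson regression in that section is not tied to ECOHIS, and the multivariate analysis concerns treatment decisions.

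The timing of the measurements is clear. Under Interventions, "a questionnaire to evaluate the impact of oral health on the quality of life of the children at baseline will be applied for the parents", and the next step is "Then, the participant will be randomly allocated in one of the two groups". Under Follow-up visits, "After 24 months, the ECOHIS will be reapplied for the children". The Outcomes section gives the measure its rank: "Other secondary outcomes will be the impact of oral health on quality of life". Allocation is stratified by age group and caries experience (Allocation: sequence generation).

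**The concern.** Subtracting the baseline score gives it a fixed weight of one, whatever its actual relation to the final score. Regression estimates that weight. Unless the best weight happens to be one, the change score carries avoidable noise.

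The rule for choosing the test is a second matter. A t test on change addresses a difference in means; Mann–Whitney addresses a rank-based contrast. If the observed distribution decides between them, nobody can say beforehand which effect the trial will report.

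Precision matters here because the Abstract states a working hypothesis that radiographs will alter patient-centred outcomes very little, and the Discussion section hopes to overturn guideline advice on bitewings. A non-significant ECOHIS result would tend to be read as support. An imprecise comparison makes such a result more likely, and a Mann–Whitney p-value alone does not show how small the effect could be.

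**Working it through.** **The plan's own figure.** The Sample size section uses SDs of 15 and 10, a difference of 5 surfaces, a two-sided 5% level and 80% power:

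n per group = (15² + 10²)(1.960 + 0.842)² / 5² = 102.04 with unrounded quantiles, so 103.

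The stated 103 is reproduced. It concerns the primary outcome. The article gives no sample size or power for ECOHIS, so 103 per arm is used below only as the number analysed.

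**Assumed inputs, not in the document.** r is the correlation of baseline with 24-month ECOHIS, s the 24-month SD, and k the baseline SD divided by the 24-month SD.

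**Variances per child.**
- Change score: s²(1 + k² − 2rk)
- Baseline-adjusted (ANCOVA): s²(1 − r²)
- Ratio, ANCOVA to change: (1 − r²)/(1 + k² − 2rk)

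The change-score term minus the ANCOVA term is (1 + k² − 2rk) − (1 − r²) = (k − r)², which cannot be negative. The ratio is therefore at most 1 and equals 1 only when k = r. With equal SDs (k = 1) it reduces to (1 + r)/2.

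**Equal SDs, 103 per arm, power for an assumed effect of 0.3 SD.**

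| r | Change, in s² | ANCOVA, in s² | Variance ratio | CI width ratio | Extra children needed by change score | Power, change → ANCOVA |
|---|---|---|---|---|---|---|
| 0.3 | 1.40 | 0.91 | 0.65 | 0.81 | 1/0.65 − 1 = 54% | 44% → 62% |
| 0.5 | 1.00 | 0.75 | 0.75 | 0.87 | 1/0.75 − 1 = 33% | 58% → 70% |
| 0.7 | 0.60 | 0.51 | 0.85 | 0.92 | 1/0.85 − 1 = 18% | 79% → 85% |

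**Unequal SDs.**
- r = 0.5, k = 1.5: 0.75/(1 + 2.25 − 1.5) = 0.75/1.75 = 0.43.
- r = 0.7, k = 0.7: 0.51/(1 + 0.49 − 0.98) = 0.51/0.51 = 1.00, so no gain.

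**The whole rule, including the Mann–Whitney branch.** This was simulated with 3,000 trials per setting and 103 per arm. The article names no normality test, so a Shapiro test in each arm at 5% was assumed. The skewed scores were rounded log-normal values limited to 0–52, with the correlation and a 0.3 shift set on the log scale. Power:

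| Scores | r | t on change | Test chosen by normality | ANCOVA |
|---|---|---|---|---|
| Normal | 0.3 | 44% | 44% | 62% |
| Normal | 0.5 | 57% | 57% | 68% |
| Normal | 0.7 | 80% | 79% | 85% |
| Skewed | 0.3 | 29% | 38% | 51% |
| Skewed | 0.5 | 38% | 50% | 57% |
| Skewed | 0.7 | 55% | 71% | 71% |

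With no true effect, every procedure rejected in 4.0% to 5.3% of trials. With normal scores the rule chose the t test in about 90% of trials and Mann–Whitney in the rest; with the skewed scores it always chose Mann–Whitney. So even for truly normal scores, about one trial in ten would report the other effect measure.

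**The case against.** The strongest reply is that the planned analysis is conventional and valid. Several stronger readings are tempting and are not supported.

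- **Bias.** A reader might infer that the change score distorts the treatment effect through chance baseline imbalance. Baseline ECOHIS precedes allocation, so the comparison is unbiased over randomisation, and the mean difference in change targets the same quantity as the adjusted mean difference. Only the Mann–Whitney branch changes what is estimated.
- **Error rate.** A reader might infer that choosing the test from the data inflates type I error. The simulation shows no inflation.
- **A gain of fixed size.** The figures of 65%, 75% and 85% need equal SDs and apply only against the t test. All children are treated between the two measurements, so equal SDs cannot be presumed. With skewed scores at r = 0.7, ANCOVA and the planned rule tie at 71%.
- **Harm to the economic analysis.** The article does not say that ECOHIS enters the cost-efficacy ratio or the quality-adjusted life years, and a Mann–Whitney test does not prevent means from being reported.
- **The only patient-reported outcome.** This is not established: pain episodes are part of the primary outcome, and the article does not say how they or the quality-adjusted life years are obtained.
- **Silence on the strata.** An article may leave this to the analysis plan, so it is not counted as a fault. Adding the strata is simply a free improvement once the model is rewritten.

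These replies narrow the point but do not remove it. The article states the method, so this is not a detail left to another document. Adjustment is never less precise in large samples than the t test on change, and the effect measure remains unfixed.

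**Conclusion.** The point holds as a matter of efficiency and of fixing the effect measure in advance; it is not one of validity. Under the usual linear model in large samples, baseline adjustment has at most the variance of the t test on change, whatever r and k are. With equal SDs and r from 0.3 to 0.7 the variance falls by 35% to 15%; with other SD ratios the reduction may be larger or nil. Against the Mann–Whitney branch the advantage in the skewed setting ran from 13 percentage points of power (51% against 38%) at r = 0.3 to none at r = 0.7. These sizes rest on assumed correlations, SD ratios, effects and score shapes, because the article gives no ECOHIS data. That the normality rule leaves the reported effect to the data follows from the text alone. No primary conclusion depends on this outcome.

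**What to change.** In Statistical methods, replace the quality-of-life sentence with a single pre-specified analysis:

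- Linear regression of 24-month ECOHIS on arm, baseline ECOHIS, age group (3–4 or 5–6 years) and caries-experience group (dmf-s up to 3 or above 3).
- Report the adjusted mean difference with a 95% confidence interval from robust standard errors or the bootstrap, to allow for skewness.
- Remove the choice of test by normality; keep Mann–Whitney at most as a labelled sensitivity analysis.

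The cost is wording only. Baseline ECOHIS and both stratification factors are already recorded before allocation, so no visit, measurement or child is added. The change should be made before the 24-month scores are compared by arm.
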